### Sample size

The nature of this innovative exploratory treatment study necessarily provides limits on the effective sample size, limiting the number of smokers that can be recruited, complete instruments, and participate in the intervention. There is not yet sufficient information to estimate a potential treatment effect size for the CBT + Yoga condition. Thus, our primary interest was to determine a valid estimate of the yoga intervention effect size for smoking cessation for a future, larger efficacy trial. Consequently, we did not conduct power analysis calculations. Rather, the required sample size was based on the number of participants needed to perform valid estimates of the CBT + Yoga intervention smoking cessation rate and possible differential smoking cessation rates between treatments. Given the typical differences in quit rates in most smoking cessation studies, often 10%-15%, [12,22,48,50], we determined that a sample size of 60 participants would be sufficient to obtain initial estimates of effect size with 60% power (medium effect size).

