### Outcomes

The primary outcomes for this study are post-treatment cessation rates, study feasibility and acceptability. Differences in post-treatment (12 week) cessation rates between conditions will provide data for estimates of effect size necessary to calculate power estimates for a major clinical trial. The qualitative and quantitative feasibility and acceptability of the Quitting in Balance program will be assessed by the following outcome measures at the individual participant level:

1. Smoking abstinence rates

2. Accrual and Retention rates

3. Acceptance of Randomization

4. Compliance with study protocol

The feasibility and acceptability outcome measures listed above will be assessed at baseline, 12-weeks (end of treatment), and 3 and 6 months follow-up.

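### The stated 60% power with 60 participants does not fit the 10-15 point quit-rate differences cited for it, and the same paragraph says no power calculation was done

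*Protocol article*

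**What the plan says.** The Sample size section of the protocol article explains that too little is known to assume an effect for yoga and that "our primary interest was to determine a valid estimate of the yoga intervention effect size for smoking cessation for a future, larger efficacy trial". It continues: "Consequently, we did not conduct power analysis calculations". The size is said to rest on what is needed to estimate quit rates and their difference.

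The closing sentence then brings in a difference and a power. It opens with "Given the typical differences in quit rates in most smoking cessation studies, often 10%-15" percent and concludes that "a sample size of 60 participants would be sufficient to obtain initial estimates of effect size with 60% power (medium effect size"). The section gives no significance level, sidedness, control quit rate or definition of *medium*.

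Two other sections bear on how the figure will be used. Under Outcomes, the post-treatment difference "will provide data for estimates of effect size necessary to calculate power estimates for a major clinical trial". Under Planned Analyses, a primary hypothesis is tested by logistic regression on quit status in all participants assigned to treatment.

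**The concern.** A power figure cannot exist without a calculation, so the paragraph contradicts itself. The sentence also sets two effect sizes side by side as if they were one: a 10-15 point difference in quit rates and a *medium* effect. With about 30 women per arm these are different quantities, and the first is mostly much the smaller.

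This matters because the trial does test an efficacy hypothesis. A reader who meets a non-significant result beside a 60% power statement would take it as moderate evidence against a 10-15 point benefit, which it would not be. The same difference is meant to inform the planning of a larger trial, so its precision at this sample size should be described correctly.

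**Working it through.** **Inputs from the article.** Total 60; stated power 60%; effect labelled *medium*; cited differences 10-15% (read as percentage points; read as relative differences they would be smaller still); binary quit outcome; all assigned participants analysed.

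**Assumptions, because the article gives no figure.** 30 per arm; 5% significance level, taken both two-sided and one-sided; control (CBT plus wellness) quit rate from 5% to 40%.

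**Step 1. Can the 60% be reproduced?** For a standardized effect of 0.5 (Cohen's d or h), power is Φ(0.5·√(30/2) − z) = Φ(1.936 − z).
- Two-sided 5% (z = 1.960): Φ(−0.024) = 49%. The exact t calculation gives 48%.
- One-sided 5%, or two-sided 10% (z = 1.645): Φ(0.292) = 61%. The exact t calculation for one-sided 5% also gives 61%.
- Chi-square with w = 0.3 and N = 60, 5% level: 64%, which is not a close match.

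So 60% is recovered for a standardized 0.5 effect with a one-sided 5% or two-sided 10% test.

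**Step 2. What is that effect in quit rates?** Solving h = 2·arcsin√p₂ − 2·arcsin√p₁ = 0.5 gives differences of 19.3, 22.8, 24.4 and 24.7 points at control rates of 10, 20, 30 and 40% (16.0 points at 5%). All lie above the cited range. Conversely, 10-15 points corresponds to h of about 0.20-0.40 at control rates of 10-40%.

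**Step 3. Power for the cited differences.** For two proportions with difference d, power = Φ[(d − z·s₀)/s₁], where s₀ = √(2·p̄(1 − p̄)/30) and s₁ = √([p₁(1 − p₁) + p₂(1 − p₂)]/30).

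Worked example, 10% vs 25%: p̄ = 0.175, s₀ = 0.0981, s₁ = 0.0962. Two-sided: (0.15 − 1.96 × 0.0981)/0.0962 = −0.44, so power is 33%. One-sided: (0.15 − 1.645 × 0.0981)/0.0962 = −0.12, so power is 45%.

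| Control rate | +10 points, two-sided | +10 points, one-sided | +15 points, two-sided | +15 points, one-sided |
|---|---|---|---|---|
| 5% | 25% | 36% | 42% | 55% |
| 10% | 19% | 29% | 33% | 45% |
| 20% | 14% | 22% | 25% | 36% |
| 30% | 12% | 20% | 22% | 33% |
| 40% | 12% | 19% | 21% | 31% |

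No cell reaches 60%. The arcsine formula gives at most 58% (5% vs 20%, one-sided). Two-sided Fisher's exact test gives 8-21% at control rates of 10-40%.

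**Step 4. What would give 60%?** With 30 per arm at two-sided 5%, the difference must be 23.5, 26.9, 28.3 and 28.4 points at control rates of 10, 20, 30 and 40% (20.5 points at 5%). Keeping the cited differences instead, the total N at control rates of 10-40% would be 250-486 for 10 points and 126-218 for 15 points.

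**Step 5. Precision with 60.** The 95% CI half-width is 1.96·s₁. At 10% vs 20% it is 1.96 × 0.0913 = 17.9 points; at 40% vs 50% it is 1.96 × 0.1278 = 25.0 points. Across control rates of 10-40% it is about 18-25 points, wider than the difference the paragraph cites.

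**The case against.** The strongest reply is that the 60% is attached to the words "medium effect size", not to the 10-15 points, and that it can be recovered for that label. That stands as far as it goes: the figure is not a slip in a formula. It does not rescue the sentence, which offers the 10-15 point range as the reason for the sample size and does not mention the one-sided 5% or two-sided 10% level needed.

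A second reply is that alpha, sidedness and control rate belong in the full protocol. That is fair, and their absence alone is no fault. The fault is that the figure fails under every combination tried for the cited differences, and that the article says it was never calculated. The missing inputs do mean that no single range can be called the true power. Control rates of about 1-3% with a 15-point difference reach 60% in some approximate formulas, but two-sided Fisher's exact test gives at most 28% there.

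Third, the study is exploratory and feasibility is among its primary outcomes. This stands and limits the severity.

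A reader might infer more, namely that the pilot estimate will often have the wrong sign and so must not be used to size the next trial. The figures and the article do not support that. At 20% vs 30%, exact binomial enumeration gives a strictly negative observed difference in 14.6% of trials, with exact ties in a further 8.0%. At 20% vs 35% and 10% vs 25% it is negative in 7.1% and 4.0%. The Outcomes section says only that the difference will supply data for later power estimates. It does not say that the point estimate alone will fix the next sample size.

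**Conclusion.** The sentence is wrong as written. The paragraph disclaims a power calculation and then reports a power, and 60 participants do not give that power for the differences cited. With 30 per arm and control quit rates of 10-40%, power for 10-15 points is about 12-33% at two-sided 5% and 19-45% at one-sided 5%. At a 5% control rate it rises to 42% and 55%, still below 60%. These ranges are conditional on the assumed allocation, significance level and control rates; none should be quoted as the trial's actual power without them. The stated 60% belongs to a larger effect under an unstated test.

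Severity is moderate. The sample size, randomization, outcome and analysis are unaffected; what changes is how a null or imprecise result is read.

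**What to change.** In the Sample size section, do one of two things:
- delete the 60% power clause; or
- restate it with its significance level, sidedness, assumed control quit rate and the detectable difference in points.

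In either case, justify 60 participants by precision: an expected 95% CI half-width of about 18-25 points for the difference, assuming 30 per arm and control quit rates of 10-40%. State that the between-arm cessation result is an estimate with a confidence interval and not a powered test. In the Outcomes section, add that the interval will accompany the estimate when it informs the later trial. Committing that later trial to a particular sizing rule is a design choice and is not needed to correct this error.

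The cost is wording only, with no extra enrolment and no change to the analysis. The downside is that the stated figure becomes less favourable.

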### Randomization

After attending an initial Orientation session, in which the study and its requirements will be explained and participants have provided written consent, participants will be randomly assigned to one of the two investigational conditions. Randomization will be conducted the first evening of the program with all participants present using a simple randomization protocol.

### Blinding

Because of the nature of the study, it is not possible to blind participants or the study counselors to condition. Smoking cessation therapy will be offered in a group setting during which time participants often remark on the content of the yoga or wellness program. Research assistants who conduct all assessments will be blind to study condition.

### Implementation

Adult women smokers who are seeking treatment for quitting smoking will be recruited through advertisements in local newspapers, flyers at grocery stores and Internet advertisements. Participants will be included in the trial if they meet inclusion criteria and have signed informed consent. To ensure the implementation of the intervention, quality audits will be conducted. A PhD clinician will listen to audio tapes of 50% of all group CBT sessions and use an objective ratings sheet to record the quality of coverage for all planned topics listed in the treatment manual.

### Time Plan

The development of this program began in August of 2007 and was finished in December 2007. Participant recruitment started in January, 2008 and continued through May 2009. The trial will be completed in June 2010.

### Planned Analyses

The primary outcome variable is quit status, verified with carbon monoxide (cutoff, 8 ppm) weekly, and with saliva cotinine (cutoff, 15 ng/ml) at the end of treatment, and both 3 and 6 month follow up assessments [49]. To be considered abstinent, subjects need to have a carbon monoxide level less than 8 ppm and a cotinine level less than 57 nmol/L [15 ng/mL].

The primary hypothesis of the study will be tested using a logistic regression to produce an odds ratio measuring the effect of CBT + Yoga on the likelihood of smoking cessation at the post-treatment and follow up assessments. The intention-to-treat principle will be used to calculate treatment effects and differences using all participants initially assigned to treatment. Analyses will also include calculations of the proportion of participants who are continuously abstinent, and abstinent as assessed for 7-day point-prevalence for both treatment groups in order to provide a fuller estimate and understanding of the possible range of the treatment effects. In addition, we will conduct a second longitudinal analysis across time (end of treatment, 3 and 6 month follow up after treatment) using the generalized estimating equations (GEE) approach of Zeger and Liang [51]. This procedure can accommodate covariates and missing data, thus allowing the maximum use of existing data (and thus enhanced power) for detecting treatment effects. This approach is also highly flexible for modeling trend analyses that allow for an alternate way to present intervention effectiveness (comparing trends in both groups over time).

Secondary analyses will examine the effects of yoga on other psychological and behavioral domains including anxiety, quality of life, spirituality, mindfulness and self-esteem. These analyses will consist of a series of repeated measures analyses of covariance using the baseline measure of each variable as a covariate and 3 repeated measurements (end of treatment, 3 and 6 month follow up).

Further analyses will examine the effects of the CBT + Yoga intervention on potential mediators of smoking behavior change, and the relationships of the potential mediators to smoking cessation. The potential mediators of interest include changes in affect, perceived stress, well being, and self-efficacy as well as cigarette craving and withdrawal symptoms. We will also examine for any differences in the effects of the CBT + Yoga intervention versus the CBT + Wellness intervention on these intermediate variables. Given the limited sample size in the proposed study, these analyses will be exploratory in nature, and within the context of these analyses, we will be trying to establish 2 of the 3 key directional effects needed to describe potential mediators as noted by Baron and Kenny [52], that is we will be investigating which of the potential mediating variables are affected by the treatment, and which of these potential mediators are also related to the key smoking cessation outcome variables. The strongest evidence for mediation is time-ordered, and these analyses will examine the effects of treatment on each of the various potential mediating variables at immediate post-treatment (8 week assessment), and include analyses of possible longitudinal treatment effects extending to the 3 and 6 month follow up. These analyses will consist of a series of repeated measures analyses of covariance using the baseline measure of each potential mediator variable as a covariate and 3 repeated measurements (end of treatment, 3 and 6 month follow up). We will conduct these analyses using Proc MIXED in SAS, which will allow us to easily conduct contrast tests to compare both between and within group effects across time. Proc MIXED also accommodates missing values under the assumption of missing at random [53], and will allow us to make maximum use of the existing data to detect treatment effects. To examine the effects of potential mediator variables on treatment outcome we will conduct a series of time-ordered logistic regressions, (e.g., post-treatment value of smoking self-efficacy, perceived stress and well-being, etc. predicting both continuous abstinence and 7-day point prevalence at 3-month follow-up).

Lastly, we will conduct qualitative analysis of the focus group material for common and emergent themes emphasizing aspects of the program that participants liked most and least, along with their suggestions for changes. Data will be coded by themes derived from the focus group guide and managed using NVivo qualitative data software. The range of participant opinions, experiences and observations will be summarized and interpreted as feedback for consideration in revising future iterations of the intervention.

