**Figure 1 F1:**
[figure not shown]
**Basic Vinyasa Yoga Asanas**.

Participants attending the wellness sessions are shown videos regarding a variety of health topics (e.g., low fat diets, breast cancer screenings, back health) followed by a discussion guided by the study RA and distribution of written material relevant to the video topic.

The CBT smoking cessation program is lead by a PhD psychologist with over 10 years experience in conducting smoking cessation groups. Treatment is delivered through use of a program manual to ensure consistent delivery of program content. Topics include self-monitoring, stimulus control, coping with high-risk situations, and stress management for smoking cessation. The program also focuses on topics of concern to women when quitting including: healthy eating, weight management, and balancing multiple roles and multiple demands. This program has been used in our prior studies [12,22]. Participants are also encouraged to select healthy, low-calorie snacks throughout the program and are provided with examples of these snacks to sample. Participants are not provided with nicotine replacement therapy (NRT) or other smoking cessation medications, but are allowed to use them in conjunction with the program, if their primary care physician deems it advisable.

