**Recruitment, Retention and Satisfaction Measures**					
Attendance and drop out		✘	✘		
Group Cohesion			✘		
Consumer Satisfaction			✘		

Each week during the program, participants are assessed for current smoking status (verified by exhaled carbon monoxide [CO]). To assess for acute changes, current positive and negative affect [48] (PANAS), nicotine withdrawal symptoms and cigarette craving are measured once weekly pre- and post-session (yoga or wellness). Smoking outcomes (7-day point prevalence abstinence) are biochemically validated by exhaled carbon monoxide (cutoff < 10 ppm) and saliva cotinine (cutoff = 15 mg/ml)[49].

At the end of each cohort, separate focus groups are to be held for the yoga and wellness participants. Focus groups are conducted by a PhD Psychologist with over 10 years experience in leading focus groups and conducting qualitative research. Focus groups discuss acceptability of the study protocols and intervention components. In particular, discussions explore participant opinions and observations regarding the intervention content, program format, and study design (e.g., program length, timing of sessions, and the number of classes per week). Each of these questions is addressed primarily from the standpoint of the individual participant's experience with the program. A qualitative data collection guide was prepared by the investigators to delineate topics and subtopics to be addressed during the focus group discussions. Each focus group requires approximately 2 hours to be completed, and is audio taped and professionally transcribed for analysis.

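### Abstinence requires low cotinine from every woman while nicotine replacement is permitted, so an abstinent user can be scored as a smoker; quit rates fall, and the arm contrast can be distorted

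*Protocol article*

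**What the plan says.** Planned Analyses names verified quit status as the primary outcome variable and defines it for all participants: "To be considered abstinent, subjects need to have a carbon monoxide level less than 8 ppm and a cotinine level less than 57 nmol/L", with 15 ng/mL given as the equivalent. CO is checked weekly. Cotinine is added "with saliva cotinine (cutoff, 15 ng/ml) at the end of treatment, and both 3 and 6 month follow up assessments".

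The text after Table 1 in Measures states the joint rule again, with a different CO limit: 7-day abstinence is "biochemically validated by exhaled carbon monoxide (cutoff < 10 ppm) and saliva cotinine (cutoff = 15 mg/ml").

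Interventions says that nicotine replacement and other cessation medications are not supplied, but that participants "are allowed to use them in conjunction with the program, if their primary care physician deems it advisable".

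Neither statement of the rule says how cotinine is to be read in a woman using nicotine replacement.

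The result feeds the main analysis. Outcomes states: "The primary outcomes for this study are post-treatment cessation rates, study feasibility and acceptability". The primary hypothesis is tested "using a logistic regression to produce an odds ratio measuring the effect of CBT + Yoga on the likelihood of smoking cessation". On the population: "The intention-to-treat principle will be used to calculate treatment effects and differences using all participants initially assigned to treatment".

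**The concern.** Cotinine is a metabolite of nicotine and cannot tell a patch or gum from a cigarette; exhaled CO can. The outcome is meant to be abstinence from smoking. Applied as written, the rule measures abstinence from nicotine in a trial that permits a nicotine product.

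A woman who has quit and uses replacement near the visit can be CO-negative and cotinine-positive. Under the intention-to-treat analysis she stays in the denominator and counts as a treatment failure. The same classification enters the logistic regression, the longitudinal GEE analysis and the mediator regressions on 3-month abstinence.

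Sample size gives a valid estimate of the yoga effect, for use in planning a larger trial, as the main interest. An error in classifying the outcome would carry into that trial's design. Participants and counselors are unblinded (Blinding) and use of replacement begins or continues after randomization, so use may differ between arms.

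**Working it through.** **The passages side by side.** The abstinence rule needs both markers to be low (Planned Analyses, repeated in Measures). A permitted co-treatment can raise one of them (Interventions). No sentence reconciles the two, so a program coded from the article would fail such a woman.

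**Inputs.** The article gives 60 participants and a typical quit-rate difference of 10 to 15 points (Sample size). It gives no expected quit rate in either arm and no rate of replacement use, so there is no plan figure on this point to reproduce. All rates below are assumptions.

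**Formula.** Let *p* be the true abstinence rate in an arm and *f* the share of true abstainers whom replacement puts above the cotinine cutoff. Then

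observed rate = *p* × (1 − *f*), and OR = [yoga rate / (1 − yoga rate)] ÷ [wellness rate / (1 − wellness rate)].

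**No true effect, 25% in both arms.**
- Equal *f*: the observed rates are equal and the OR is 1.00.
- *f* = 10% yoga, 30% wellness: 0.25 × 0.90 = 22.5% and 0.25 × 0.70 = 17.5%. OR = (0.225/0.775) ÷ (0.175/0.825) = 1.37.
- The reverse: OR = 1/1.37 = 0.73.

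**A true effect, 20% wellness and 35% yoga** (15 points, the top of the article's range; the 20% is assumed).

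| *f* wellness / yoga | Observed wellness / yoga | Difference | OR |
|---|---|---|---|
| 0% / 0% | 20% / 35% | 15 points | 2.15 |
| 20% / 20% | 16% / 28% | 12 points | 2.04 |
| 30% / 30% | 14% / 24.5% | 10.5 points | 1.99 |
| 10% / 30% | 18% / 24.5% | 6.5 points | 1.48 |
| 30% / 10% | 14% / 31.5% | 17.5 points | 2.82 |

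With equal *f* the risk ratio stays at 35/20 = 28/16 = 1.75, but the difference shrinks by the factor (1 − *f*) and the OR moves toward 1. With unequal *f* the OR can fall on either side of the true 2.15.

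**Scale.** Taking 30 women per arm, one misclassified woman moves an arm's rate by 1/30 = 3.3 points, and a 10 to 15 point difference is 3 to 4.5 women.

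**The case against.** The strongest reply is that harm to the comparison is conditional. The rule loses some true quitters and adds no false ones. If use among abstainers is equal across arms, a null OR stays at 1.00 and a real effect is only mildly reduced (2.15 to 2.04 at 20%). This stands. A reader might infer that the arm contrast is biased as a matter of fact, but the documents do not support that. An unblinded design makes unequal use possible; nothing shows that it occurs.

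A reader might also infer that replacement use is common at end of treatment, and so that many points of abstinence are lost. The article gives no uptake figure, and replacement is neither supplied nor used without a physician's agreement. The same permission covers other cessation medications, and those without nicotine do not raise cotinine. Nor does every user necessarily exceed the cutoff. This stands too: no size can be asserted.

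Nor should it be inferred that replacement use goes unrecorded. Table 1 lists smoking behavior at every assessment without its items, and a condensed article may leave those to the full protocol.

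Finally, the trial is a pilot. In the 22.5% versus 17.5% illustration, with 30 per arm, the 95% half-width for the difference is 1.96 × √(0.225 × 0.775/30 + 0.175 × 0.825/30) = 20 points, against a 5-point artefact. That puts the size in proportion, but imprecision does not excuse a systematic error in an outcome rule that can be put right cheaply.

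**Conclusion.** The point holds as a wrong rule, not as a missing detail: the article states an explicit definition, twice, and it conflicts with a co-treatment that the article permits. Once any abstainer exceeds the cutoff because of replacement, the quit rate in her arm is biased downward. A true difference is then attenuated on the risk-difference and OR scales even with equal use, while the risk ratio is unchanged. The contrast can be biased in either direction if use differs by arm.

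The amount is unknown. The OR of 1.37 or 0.73 under no effect rests on an assumed 25% abstinence and an assumed 10% versus 30% split, and the table rests on equally assumed rates. They show what the rule can do, not what it will do. The conclusion also relies on the general fact, not stated in the article, that cotinine reflects nicotine from any source.

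**What to change.** In the outcome definition:

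- For women reporting current nicotine-replacement use at end of treatment, month 3 or month 6, verify self-reported abstinence by CO alone. Keep CO plus cotinine for all others.
- Use one CO cutoff. Measures has below 10 ppm and Planned Analyses below 8 ppm; these must be reconciled first, because CO becomes decisive for users. The same edit should correct the cotinine unit (mg/ml in Measures, ng/ml in Planned Analyses).
- Report two sensitivity analyses: the strict both-tests rule for everyone and a CO-only rule for everyone.
- Tabulate replacement use by arm at each visit.

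The cost is a few sentences and, if use is not already asked, one survey item. Time Plan describes recruitment as having run through May 2009, so a new item may come too late for some end-of-treatment visits. Where use was not recorded, the CO-only analysis needs no new data, since Table 1 schedules CO at every assessment.

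There is a real downside. Verification becomes less strict for users and depends on self-reported use in an unblinded trial; if use differs by arm, undetected smoking could differ by arm too. The two sensitivity analyses let a reader judge this. The change concerns outcome classification only and leaves treatment as it is.

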## Methods/Design

### Design

The study design is a randomized, controlled pilot study comparing two conditions: 1) group-based cognitive-behavioral therapy (CBT) for smoking cessation plus a twice-weekly group-based yoga program (***Yoga***); and 2) CBT for smoking cessation plus a group-based wellness program that serves as a contact-control (***Wellness***). Groups of 8-10 individuals enter the program in sequential cohorts and participate in the 8-week treatment program. Assessments take place at baseline (before program entry), end-of-treatment (week 8), and both 3 and 6 months follow up.

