### Procedures

Enrolled participants are randomly assigned to either the yoga or wellness arms of the study. All participants are also provided on a weekly basis with 1-hour of group based CBT for smoking cessation (separate groups are held for yoga and wellness participants). One yoga and one wellness session per week are scheduled for the same night as the smoking group treatment, so that participants need to travel to the program only two evenings per week.

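### Women are treated in arm-specific groups, but no planned model accounts for therapy group, so the uncertainty of the yoga effect is understated if outcomes correlate within groups

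*Protocol article*

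**What the plan says.** All treatment is delivered in groups. The Design section compares CBT "plus a twice-weekly group-based yoga program" with CBT "plus a group-based wellness program that serves as a contact-control". CBT is common to both arms, yet the Procedures section says that "separate groups are held for yoga and wellness participants". On intake, the Design section says: "Groups of 8-10 individuals enter the program in sequential cohorts and participate in the 8-week treatment program". The Randomization section says: "Randomization will be conducted the first evening of the program with all participants present using a simple randomization protocol". It states no block, stratum or minimum group size.

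Under Planned Analyses, the primary test is stated as follows: "The primary hypothesis of the study will be tested using a logistic regression to produce an odds ratio". Next comes the GEE: "we will conduct a second longitudinal analysis across time (end of treatment, 3 and 6 month follow up after treatment". For the repeated-measures analyses of covariance on mediators, with the baseline value as covariate: "We will conduct these analyses using Proc MIXED in SAS". No section names therapy group or cohort as a random effect, cluster, covariate or stratum. The Sample size section makes no allowance for clustering and gives no ICC.

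**The concern.** This is an individually randomized trial with group treatment. For eight weeks, women allocated together to one arm share their peers and every CBT and adjunct session. Their quit outcomes may therefore be correlated, and the measurement schedule itself includes group cohesion. A logistic regression without a group term takes 60 women as 60 independent observations. The GEE is described as an analysis over time, which addresses repeated visits by the same woman. It does not address correlation between women in one group. The mixed model as described has the same gap.

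With positive within-group correlation, the standard error of the yoga effect is too small. The Outcomes and Sample size sections give the pilot's purpose as an effect-size estimate for planning a larger trial, so understated uncertainty would carry into that trial's planning.

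A second point follows from the same design. If 8-10 is the whole cohort, unrestricted allocation can leave one arm with too few women to form a working group.

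**Working it through.** **The plan's own figure.** The Sample size section gives 60% power with 60 women for a medium effect. Taking medium as d = 0.5 (a convention, not stated) and 30 independent women per arm, power = Φ(d·√(30/2) − z).
- One-sided 5%: Φ(1.936 − 1.645) = 61.5%.
- Two-sided 5%: Φ(1.936 − 1.960) = 49.1%.

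The stated 60% is thus matched by a one-sided 5% (or two-sided 10%) test with independent women.

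**Number and size of groups.** The text allows two readings of 8-10.
- Whole cohort (the literal reading): 60/10 to 60/8 gives about 6-8 cohorts, 12-16 arm-specific groups and a mean size m of 4-5.
- Each arm's group: 16-20 women per cohort, about 3-4 cohorts, 6-8 groups and m of 8-10.

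**Effect of ignoring the groups.** Design effect DE = 1 + (m − 1)·ICC. The true standard error is √DE times the independent-data one. Effective N = 60/DE. The true two-sided type I error of a nominal 5% test is 2·[1 − Φ(1.96/√DE)]. The ICC is assumed.

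| m | ICC | DE | SE multiplier | Effective N | Type I error |
|---|---|---|---|---|---|
| 4 | 0.01 | 1.03 | 1.015 | 58.3 | 5.4% |
| 5 | 0.02 | 1.08 | 1.039 | 55.6 | 5.9% |
| 4 | 0.05 | 1.15 | 1.072 | 52.2 | 6.8% |
| 5 | 0.05 | 1.20 | 1.095 | 50.0 | 7.4% |
| 5 | 0.10 | 1.40 | 1.183 | 42.9 | 9.8% |
| 8 | 0.01 | 1.07 | 1.034 | 56.1 | 5.8% |
| 10 | 0.05 | 1.45 | 1.204 | 41.4 | 10.4% |
| 10 | 0.10 | 1.90 | 1.378 | 31.6 | 15.5% |

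A beta-binomial simulation (40,000 runs, assumed quit rate 25%, pooled two-proportion test standing in for the unadjusted logistic regression) agrees. For groups of 4-5 it gives 5.5-10.4% over ICC 0.01-0.10, and 5.1-5.2% at ICC 0. For m = 4-5, the one-sided power of 61.5% falls to between 60.4% (ICC 0.01, m = 4) and 49.7% (ICC 0.10, m = 5).

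**Small groups, whole-cohort reading.** Under simple 1:1 allocation of n women, P(one arm has two or fewer) = 2·[C(n,0) + C(n,1) + C(n,2)]/2ⁿ.
- n = 8: 2·37/256 = 28.9%.
- n = 9: 2·46/512 = 18.0%.
- n = 10: 2·56/1024 = 10.9%.

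The chance of at least one such group in the trial is 1 − (1 − p)^C: 94% for 8 cohorts of 8, 75% for 7 cohorts of 9, and 50% for 6 cohorts of 10.

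**Small groups, per-arm reading.** With 16-20 women per cohort, the chance is at most 0.4% per cohort and under 2% over the trial.

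**The case against.** The strongest objection is that the size rests wholly on an assumed ICC. This stands. At ICC 0.01-0.02 with groups of 4-5, the true standard error is only 1.5-4% larger. A reader might infer that the intervals are certainly, and materially, too narrow. The document shows only that the models would understate uncertainty if the ICC is positive.

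The mechanism can also be overstated. Season is common to both arms of a cohort, and variation shared by both arms does not make the unadjusted standard error too small. The Interventions section suggests common leaders, a manual for CBT and a consistent yoga sequence, and the Implementation section adds quality audits. What remains is variation between arm-specific groups, chiefly peers and group dynamics.

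A reader might also infer that groups of one or two women must have occurred, or that allocation should be changed now. The document supports neither. The small-group risk needs the whole-cohort reading and nearly vanishes on the other, where the clustering effect is larger; the two worst cases cannot be added together. The Time Plan has recruitment continuing through May 2009, so probably no cohort is left to randomize.

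A third objection is that a journal article names model families, and a group term could sit in a plan not shown. That is possible. But the article does state the primary model, and as stated it assumes independent women. Nor does the generic remark that GEE accommodates covariates and missing data supply a group term.

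Finally, this is a pilot, so type I error matters less than in a confirmatory trial. That is fair, but an honest interval around the effect estimate is what a pilot is meant to supply.

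**Conclusion.** The point holds in conditional form. Treatment is delivered in arm-specific groups, and the logistic, GEE and mixed models as described carry no therapy-group term. For any positive correlation between women in the same group, the stated analysis understates the standard error of the yoga effect. The direction is firm; the size is not, because it depends on an ICC that the document does not give.

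Over an assumed ICC of 0.01-0.10, type I error is about 5.4-9.8% with groups of 4-5, and about 5.8-15.5% if 8-10 is each arm's group. The risk of an arm with two or fewer women is real only on the whole-cohort reading, and it is mainly a lesson for the larger trial. The analysis should be corrected, but nothing here invalidates the pilot.

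**What to change.** - **Models.** Define therapy group as cohort by arm. Add a random intercept for it to the logistic and mixed models. Cluster the GEE on therapy group with a small-sample-corrected variance. Refer the yoga effect to a t distribution with degrees of freedom based on the number of groups.
- **No fixed cohort effects.** With 6-8 cohorts they would add 5-7 parameters. At an assumed 25% quit rate there are only about 0.25 × 60 = 15 quitters.
- **ICC.** Report it with its confidence interval as descriptive only. About 12-16 groups estimate it poorly: in a simulation of 12 groups of 5 with a true ICC of 0.05, the estimate was zero or negative in 35% of runs.
- **Meaning of 8-10.** State whether it is the whole cohort or each arm's group. If it is the whole cohort, balance allocation within cohort for any cohort not yet randomized and in the larger trial.

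The cost is wider intervals. With 12-16 groups and degrees of freedom of groups minus two (10-14), t is 2.23-2.14 instead of 1.96, so intervals are about 9-14% wider before any design effect. With 6-8 groups (4-6 degrees of freedom), t is 2.78-2.45 and the widening is about 25-42%. The only data needed are each woman's cohort and arm.
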